**Pain**

Changes in NP intensity will be measured using the ISCIPBDS 3.0 pain intensity scale (
Widerstrom-Noga *et al.*, 2023). Changes in NP interference as measured in the ISCIPBDS 3.0 pain interference scale and changes in neuropathic pain symptoms will be assessed using the Neuropathic Pain Symptom Inventory (
Bouhassira *et al.*, 2004;
Wong *et al.*, 2020). In addition, we will use resting EEG as a biomarker for chronic NP. All pain related outcomes will be measured at three timepoints: baseline (week 1/Timepoint 1 (T1)), post intervention (week 13/Timepoint 2 (T2)) and at 6-month follow-up (Timepoint 3 (T3)).

**Health Related Quality of Life (HRQoL)**

We will assess HRQoL using the EUROQOL EQ-5D-5L (
Herdman *et al.*, 2011) at baseline, post-intervention and 6-month follow-up.

### Qualitative study

Qualitative focus group discussions with participants and interventionists will be conducted following the intervention to ascertain their experiences of the ExSCIP programme. As pain is multidimensional and often influenced by factors such as attitudes, self-efficacy and thoughts, inclusion of a qualitative study is important to inform additional development and improvement to the intervention.

The qualitative semi-structured question schedule will be developed in collaboration with our PPI panel. A person unknown to the participants will complete the exit discussions. Key areas to be discussed will be:

satisfaction with and acceptability of the ExSCIP programme,perceptions of exoskeleton use (positive and negative)barriers and facilitators to attendance, implementation and continuation of the intervention.perceptions of pain assessment tools and whether they feel it captures their pain.

Qualitative feedback will also be obtained from staff who delivered the ExSCIP intervention to evaluate physiotherapists’ perspectives of delivering an exoskeleton walking programme for pain, with questions addressing.

BeliefsViews on implementationTherapist burdenSkill level required to deliver an intervention of this nature.

Qualitative analysis will be underpinned by the principles of phenomenology: open-ended responses from focus group discussions and debriefing interviews will be subject to reflexive thematic analysis. Audio recorded data will be transcribed verbatim by an independent person and transcripts read by two researchers independently. Participant research codes will be used in transcription.

### Data/statistical analysis

Baseline demographics of group participants will be presented in two manners. Categorical data will be presented as frequencies & percentages. Continuous data will be presented as means & standard deviations. If there is evidence of skew in continuous data, mean and standard deviation (SD) will be substituted with median and interquartile range.

Outcome variables will be assessed at three time points (baseline, week 13, 6 month follow up). Health related quality of life (HRQoL) as assessed by the EQ-5D-5L will be converted from value scores to index scores for each item which will allow for calculation of a collated index score (
Hobbins *et al.*, 2018). Pain intensity, pain interference and HRQoL index scores will be presented as mean and SD at each time point. Within group mean differences and 95% confidence intervals (95% CI) will be calculated at week 13- and 6-month follow-up compared to baseline. Between group differences at each time point will be calculated using repeated measures ANOVAs. The effect sizes of between group differences will be assessed using ETA squared/Omega squared statistics. Statistical significance will be determined α-priori at an alpha level of 0.05. Statistical analysis will be undertaken using IBM SPSS version 29 (
IBM, 2023) and conducted as intention-to-treat and per-protocol. Alternatively, this statistical analysis can be performed using the open access R software (
R core team, 2024).

Exploratory EEG data analysis will use a multilevel linear mixed model (LMM) to examine differences between the intervention groups over time in the EEG alpha, beta and theta band power. Repeated measures within participants will be modelled as a random effect. Fixed effects in the model, will include group assignment and time. The moderating effects of pain intensity and interference will also be evaluated. The LMM will study both main effects and interaction effects using the R package lme4 (
Bates *et al.*, 2015) to fit the models. Models will be compared using Likelihood Ratio Tests (LRT) to assess the significance of effects.

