### Sample size, randomisation, and blinding

As ExSCIP is a feasibility trial, a sample size calculation will not be conducted. The trial aims to recruit 20 participants to the intervention arm and 20 to the control arm, retaining at least 32 at follow-up. Due to practical considerations including traumatic SCI being a rare condition in Ireland, the strict eligibility criteria in addition to the precedent set by previous RCT’s in this area with considerably smaller sample sizes (
Martinez *et al.*, 2018), this number is considered adequate to inform whether sufficient participants can be recruited and retained in the study and to evaluate the feasibility goals outlined.

Following informed consent and baseline evaluation for exoskeleton, recruited participants will then be randomly allocated to the intervention group (ExSCIP) or to the comparator group (receiving a blended relaxation programme devoid of motor imagery). This will be completed by an independent gatekeeper based in the UCD Centre for Support and Training in Analysis and Research (CSTAR), using a pre-generated electronic randomisation schedule stratified by NP severity. Allocation disclosure will be made by telephone by the independent gatekeeper in CSTAR to the trial interventionist after informed consent and baseline evaluation.

To minimise potential biases, all assessments and outcome measures (baseline, post intervention and 6-month follow-up) will be taken by an independent assessor blinded to the treatment allocation. The data analyst will also be blinded to the intervention allocation.

Blinding participants to the ExSCIP intervention is not feasible. The hypothesis of the study will be masked however in the information to subjects. Participants will be informed that the trial is comparing two types of treatment, to avoid higher expectations in the ExSCIP group.

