### Outcomes

**
*Primary outcomes*
**

The primary outcomes will focus on trial feasibility. Full details of these and progression criteria to a multicentre, international RCT can be found in
Table 2:

**Table 2. T2:** Feasibility Outcomes and Progression Criteria.

Feasibility Outcomes	Progression Criteria
Number of individuals who contact researchers about the trial.	Successful intervention uptake, with recruitment rates of ≥35% of individuals deemed eligible following in-person assessment and at least 20 individuals randomised to the two arms.
Recruitment rates disaggregated by SII and NRH channels (recruitment capacity at named sites).	Loss to follow-up/attrition rates < 20%.
Number of individuals screened by phone.	Qualitative data that indicates that ExSCIP is an acceptable intervention to individuals with NP following SCI and to physiotherapists delivering the intervention, where no insurmountable barriers were identified.
Number of individuals who are eligible to proceed to in person-assessment following phone screening.	Safe implementation of the ExSCIP intervention: no serious adverse events
Number of individuals who consent to participate in the study following phone screening.	Average programme adherence of ≥ 80% of all sessions.
Trial uptake rates.	A non-inferior effect for NP intensity is observed in the intervention arm in comparison to the control arm.
Number who are eligible to participate in the study after in-person assessment.	A Minimal Clinically Important Difference (MCID) for NP intensity in an SCI population (1.74 points decrease on NRS) is observed within the 95% confidence interval for mean change for the intervention arm ( Farrar *et al*., 2001).
Number randomised to participate in the study.	
Adherence with the 12-week exoskeleton walking programme (attendance and total number of steps taken)	
Any safety/adverse events.	
Feasibility of stratified randomisation	
Number who are lost to follow up at week 13 and 6-month follow up.	
Feasibility of assessment procedures.	
Time needed to collect and analyse data.	

**
*Secondary outcomes*
**

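### The repeated-measures ANOVA planned for pain and HRQoL is inefficient, in its usual form keeps only people with all three visits, and gives no signed between-arm difference for the non-inferiority progression criterion

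*Protocol article*

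**What the plan says.** The Data/statistical analysis section of the protocol article sets the times: "Outcome variables will be assessed at three time points (baseline, week 13, 6 month follow up". It gives means and SDs at each time, and 95% CIs for within-group change from baseline. For the comparison of arms it says "Between group differences at each time point will be calculated using repeated measures ANOVAs". Effect sizes for that comparison are eta or omega squared, and "Statistical significance will be determined α-priori at an alpha level of 0.05". The analysis is to be "conducted as intention-to-treat and per-protocol", in SPSS or alternatively in R. No covariate is named. The same section plans a linear mixed model with a random participant effect, but only for the exploratory EEG data.

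The section on sample size, randomisation and blinding states "The trial aims to recruit 20 participants to the intervention arm and 20 to the control arm, retaining at least 32 at follow-up", and allocation is made "using a pre-generated electronic randomisation schedule stratified by NP severity". Among the progression criteria in Table 2 (Outcomes) are "Loss to follow-up/attrition rates < 20" per cent and a criterion that the intervention arm be non-inferior to control on neuropathic pain (NP) intensity.

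**The concern.** Three features of the named analysis matter.

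- **Incomplete visits.** Classical repeated-measures ANOVA, as in the SPSS general linear model procedure, needs every repeated value for a person. One missing visit removes that person from every comparison. The plan tolerates appreciable loss and also claims an intention-to-treat analysis.
- **Baseline used as an outcome, not a covariate.** The baseline score is usually the strongest predictor of a later pain score. It is available for everyone and would sharpen the comparison of arms at no cost in data.
- **Form of the result.** Eta squared, omega squared and an omnibus F-test say how much variance is explained. They do not say which arm did better or by how much.

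At stake are precision in a 40-person trial, possible selection bias at week 13 if later drop-out is related to pain, and a usable between-arm estimate for the progression decision and for designing the definitive trial.

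**Working it through.** **Inputs from the protocol article.** 40 randomised, 20 per arm; at least 32 retained; three outcome times including baseline.

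**Inputs assumed, because the article does not give them.** The correlation r between baseline and follow-up score (0.4 to 0.7); equal SD at each visit; the split of losses before and after week 13.

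**1. The plan's own figure.** 40 × (1 − 0.20) = 32, so the retention target allows 40 − 32 = 8 losses. Eight of 40 is exactly 20%, which meets the retention target but not the strict progression criterion of under 20%. The largest loss meeting that criterion is 7.

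**2. Cost at week 13 of requiring all three visits.** With balanced arms the standard error is proportional to 1/√N, so the inflation is √(N seen at week 13 / N with all visits).

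| Losses by week 13 | Losses after week 13 | Seen at week 13 | Complete | SE ratio |
|---|---|---|---|---|
| 0 | 8 | 40 | 32 | √(40/32) = 1.12 |
| 4 | 4 | 36 | 32 | √(36/32) = 1.06 |
| 8 | 0 | 32 | 32 | 1.00 |

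The first row is the ceiling for 8 losses in all.

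**3. Effect of baseline adjustment.** With n per arm and SD σ, the variance of the between-arm difference at one visit is:

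- post-only: 2σ²/n
- change from baseline: 2σ² × 2(1 − r)/n
- baseline-adjusted: 2σ²(1 − r²)/n

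The adjusted variance is therefore (1 − r²)/[2(1 − r)] = (1 + r)/2 of the change variance, and 1 − r² of the post-only variance.

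| r (assumed) | relative to change, (1 + r)/2 | relative to post-only, 1 − r² |
|---|---|---|
| 0.4 | 0.70 | 0.84 |
| 0.5 | 0.75 | 0.75 |
| 0.7 | 0.85 | 0.51 |

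The two columns are alternatives, since only one comparator can apply to a given estimate. Under these formulas, which ignore the degree of freedom spent on the covariate, both ratios are below 1 for any r strictly between 0 and 1.

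**4. Whether deletion could bias week 13.** A simulation of 4,000 trials used 20 per arm, SD 2, r = 0.5 and a true difference of −1.74 at both follow-ups. Loss at 6 months rose with week-13 pain in the intervention arm and was a random 20% in the control arm. About 31 people were complete. The mean week-13 difference was −2.39 among completers, −2.23 among completers with baseline adjustment, and −1.74 using everyone seen at week 13, with or without adjustment. The bias in this example therefore comes mainly from deletion. It illustrates one assumed mechanism and does not estimate bias in this trial.

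**5. Whether the output can serve the criterion.** Non-inferiority needs a signed difference between arms and a bound on it. Eta and omega squared are unsigned, and the omnibus F-test is non-directional. The confidence intervals the section names are for change within each arm.

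**The case against.** The strongest reply is that much of this is inference. The article does not say that incomplete cases are dropped. Imputation before the ANOVA, or some R routines, would fit its wording, and an analysis plan not shown may settle missing data and covariates. This stands: a reader might infer that the analysis contradicts intention-to-treat outright, but the text supports only a conditional statement about the method's usual behaviour. The stratum limb is the weakest. Covariates are often left to the analysis plan, and since the severity groups are described by cut-offs on the baseline pain score, adjusting for that score would recover most of the information.

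A reader might also infer that including baseline dilutes a constant effect d to 2d/3. That applies to a group main effect averaged over three visits. The article speaks of differences at each time point, and a time-specific contrast is not diluted. Having baseline among the repeated measures is not in itself an error either.

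The 1.12 factor should not be read as the expected loss. The article says only "retaining at least 32 at follow-up", and people lost before week 13 would add no follow-up data under any model.

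Finally, pain is a secondary outcome and no power is claimed. Of the seven progression criteria in Table 2, five do not use pain scores and one uses the within-arm CI that the plan does supply. This limits the weight of the point. It does not answer the mismatch between the stated effect measures and the one criterion that compares pain between arms.

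**Conclusion.** The point holds as a recommended change to a secondary analysis that feeds one progression criterion. It does not threaten the feasibility outcomes that are the trial's primary question.

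What the article fixes is the ANOVA over three times and the unsigned effect sizes; those effect sizes cannot support the non-inferiority criterion whatever is done about missing data. What is conditional is the loss of week-13 data. Without imputation it would inflate the week-13 standard error by at most 1.12 with 8 losses, by 1.06 if half of them fall after week 13, and not at all if none do. The gain from baseline adjustment is certain in direction for r between 0 and 1, apart from the small cost in degrees of freedom. Its size depends on r, which the article does not give, and on the comparator.

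**What to change.** Analyse pain intensity, pain interference and HRQoL with a linear mixed model:

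- outcomes: week 13 and 6 months;
- fixed effects: arm, time, arm-by-time, baseline score and NP-severity stratum;
- within-participant correlation modelled by a random participant effect or an unstructured covariance;
- small-sample degrees of freedom, for example Kenward–Roger;
- all randomised participants with any follow-up value, analysed in the arm allocated.

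Report the adjusted between-arm difference at each time with its 95% CI in place of eta or omega squared, and judge the non-inferiority criterion from that interval.

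The cost is a change of wording. The variables are already collected, and a mixed model is already planned for EEG. There are small downsides. The model relies on data being missing at random. People with no follow-up value still contribute nothing, so their number and reasons should be reported. With about 40 participants the covariance structure and degrees of freedom need care, and the overlap between baseline pain score and stratum should be acknowledged. The study is described as ongoing, so the change should be made before unblinded data are seen.

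### The likelihood ratio tests for the exploratory EEG mixed models, if referred to chi-square as is usual, run somewhat above 5%: about 6% for group-by-time and up to about 11% for plausible pain-moderation tests

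*Protocol article*

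**What the plan says.** The protocol article, section Data/statistical analysis, sets out the EEG analysis: "Exploratory EEG data analysis will use a multilevel linear mixed model (LMM"), applied to alpha, beta and theta band power. Group and time are fixed effects, participant is a random effect, and both main effects and interactions are studied in lme4. On moderation it says: "The moderating effects of pain intensity and interference will also be evaluated". On testing it says: "Models will be compared using Likelihood Ratio Tests (LRT) to assess the significance of effects". The preceding paragraph, on pain and quality of life, sets the level: "Statistical significance will be determined α-priori at an alpha level of 0.05". The level is not repeated for EEG.

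The section Sample size, randomisation, and blinding gives the numbers: "The trial aims to recruit 20 participants to the intervention arm and 20 to the control arm, retaining at least 32 at follow-up". There are three time points.

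The article does not give the reference distribution of the likelihood ratio statistic. It also does not say whether pain enters as a baseline or a time-varying covariate, whether the two pain measures enter separately or together, or which interactions are tested.

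**The concern.** A likelihood ratio test of fixed effects compares two maximum-likelihood fits. Its chi-square reference is a large-sample result that makes no allowance for the degrees of freedom spent on fixed effects. With few participants the statistic is therefore too large on average. The excess grows with the number of fixed effects in the model and with the number tested together.

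Moderation by pain adds the most terms, so it is affected most. It is also the analysis that would link EEG to pain in an intervention described as mechanism-based. A spurious signal there could shape the hypotheses carried into the definitive trial.

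**Working it through.** **Inputs from the protocol article.** N = 40 randomised (20 + 20), at least 32 retained; three visits; nominal level 0.05; one random effect per participant.

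**Assumptions.** A random intercept, balanced data, and a chi-square reference. The moderation models below are possible readings, because the article does not write one out. It gives no error-rate figure to reproduce.

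**Closed form.** In the balanced random-intercept model (ignoring the boundary at zero variance), effects that vary within participants are tested in a stratum with n = 2N observations. Effects between participants are tested in one with n = N. With p fixed-effect parameters in the stratum and q of them tested,

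LR = n · log(1 + qF/(n − p)), where F follows F(q, n − p) under the null.

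The chi-square test rejects when LR > c, the 95% point of chi-square with q df. That is the same as F > F* = (exp(c/n) − 1)(n − p)/q, so the true size is P(F(q, n − p) > F*). Check: with n = 1,000,000, p = 4 and q = 2 the formula returns 5.00%.

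**Group-by-time, N = 40.** n = 80, p = 4, q = 2, c = 5.991. F* = (exp(5.991/80) − 1) × 76/2 = 2.955. The correct 5% point of F(2,76) is 3.117. Size = P(F(2,76) > 2.955) = 5.8%.

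**Group-by-time, N = 32.** n = 64, F* = (exp(5.991/64) − 1) × 60/2 = 2.944, against 3.150 for F(2,60). Size = 6.0%.

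**Other tests by the same formula:**

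| Test | p | q | N = 40 | N = 32 |
|---|---|---|---|---|
| Group × time | 4 | 2 | 5.8% | 6.0% |
| Group × one pain measure (between participants) | 4 | 1 | 6.5% | 6.9% |
| Group × time × one pain measure | 8 | 2 | 6.7% | 7.3% |
| Group × time × pain, both measures jointly | 12 | 4 | 8.5% | 9.7% |
| All within-participant pain terms, both measures | 12 | 8 | 8.9% | 10.2% |
| All pain-by-time terms, model saturated in group, both pain measures and time | 16 | 12 | 11.3% | 13.8% |

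**Simulation.** Maximum-likelihood random-intercept fits were run under the null: 3,000 datasets per setting, intraclass correlation 0.5 (assumed), Monte Carlo standard error about 0.4 to 0.6 percentage points. Settings were 40 complete, 40 with 8 dropouts, and 32 complete, each with baseline and with time-varying pain. Rejection rates across the six settings:

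- group × time: 5.5% to 6.2% (5.9% to 6.2% with 40 randomised and 8 dropouts)
- group × time × one pain measure: 6.6% to 7.8%
- all six terms of one pain measure together: 7.4% to 8.8%
- group × time × pain for both measures (4 df): 7.9% to 10.6%
- all twelve terms of both measures together: 9.8% to 13.0%

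The simulation agrees with the closed form. Every rate is above 5%, and the excess grows with the size of the model.

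**The case against.** The strongest reply is that the article never says chi-square. It says only that likelihood ratio tests will be used, and a parametric-bootstrap reference would fit that sentence. The reference distribution and the moderation model could also be settled in an analysis plan that is not shown. This stands, and it makes the point conditional. It does not remove the point: the article names the test and its purpose, and the usual form of that test on lme4 fits is the chi-square one.

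A second reply is that little depends on it. The analysis is labelled exploratory, Table 2 contains no EEG progression criterion, and the group-by-time excess is about one percentage point. This stands too, and it sets the severity.

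A third is that 32 complete cases is the pessimistic end, because the mixed model also uses the partial data of participants who drop out. That is right, but the excess is present at 40 as well.

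Two stronger readings are tempting, and the documents support neither. A reader might infer that moderation tests run at about 14%, nearly three times the nominal rate. In the closed form, a rate near that (13.8%) needs a 12-df omnibus test in a saturated model with only 32 participants, and the protocol describes no such test. A reader might also infer that band power will be analysed untransformed, at a cost in power. The article names the outcome but neither states nor rules out a transformation, and any power figure would rest on variances and effects that it does not give.

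**Conclusion.** The point holds as a conditional and minor one. If the likelihood ratio statistic is referred to chi-square with 32 to 40 participants and three visits, the true error rate at a nominal 5% is:

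- about 6% for group-by-time
- about 6.5% to 7.5% for moderation by one pain measure
- about 8% to 11% for plausible tests involving both measures.

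The direction is the same in every setting checked. The sizes rest on a random-intercept model and on assumed moderation models, and they assume that the 0.05 level is meant to apply to EEG. The feasibility outcomes and the progression decision are not affected.

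**What to change.** Replace the likelihood ratio sentence with, for example: *Fixed effects will be tested with F-tests using Kenward-Roger (or Satterthwaite) degrees of freedom from REML fits, or with a parametric-bootstrap likelihood ratio test, on the same lme4 models.*

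For balanced data the group-by-time test then becomes F(2,76) with 40 participants or F(2,60) with 32, and it is exact under the random-intercept model. Kenward-Roger and Satterthwaite were not themselves simulated here; the claim of exactness is for the balanced F-test.

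The cost is one sentence and standard add-on R functions. No new data or change in sample size is needed, and p-values become slightly larger.
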